### US Census Bureau Data

We will gather publicly available data about jurisdictions (eg, characteristics and demographic information) from the US Census Bureau website. Using the Census’s search and filtering functions, we will extract relevant data at the appropriate geographic level (eg, state or county). These data will include distributions of educational attainment, poverty status, insurance coverage, and race and ethnicity composition, each of which will be used to examine jurisdictional differences and their associations with PrEP uptake.

### Other Data Sources

Other potential sources of data may be incorporated into analyses as they become available over time.

#### Primary Outcome Measures

When possible, we will use PrEP outcomes that have been previously defined in prior literature [7,8,17,24-30]. Given a range of analyses across objectives 1-3 that include exploratory, quasi-experimental, and modeling that will require different time horizons and levels of aggregation, we anticipate a number of different PrEP outcomes across analyses for this research program. When appropriate, we will assess PrEP use in terms of starts and retention. PrEP starts will be defined as the number of persons starting PrEP per 100,000 population (PrEP starts per capita). For monthly assessments of this outcome, a PrEP start is defined as a person initiating PrEP for the first time or reinitiating PrEP after a lapse in prescription of a cut point, such as at least 1 month, calculated from the biweekly proportion of days covered (PDC) reaching 0.57 or lower (eg, less than 4 days per week). PDC measures the percentage of days that filled medication prescriptions could provide coverage for a period if the medication is taken as prescribed. The PDC metric has been commonly used in PrEP studies [24,25,27,28,31] and has been suggested as a good metric for studies focusing on PrEP use at specific time points [24]. We will conduct sensitivity analyses to assess the impact of different cut points for lapses in coverage. For retention in care, all PrEP fills not classified as PrEP starts will be considered prescriptions obtained while retained in PrEP care. PrEP retention will be defined as consecutive PrEP prescription refills based on their PrEP modalities, calculated as the time period in continuous PrEP care. For analyses that aggregate beyond the monthly level, such as yearly analyses, we will use definitions previously used in the literature and by the CDC. For yearly analyses, this involves counting any people with a prescribed day of PrEP in that calendar year, including persons with sufficient pills prescribed in the prior year to have days prescribed in the following year [3,8]. We will also analyze how PrEP is used relative to need by assessing the number of persons using PrEP per new HIV diagnosis (PnR). For models in objective 3, the primary outcomes will be HIV infections averted and cost-effectiveness.

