## Methods

### Research Setting and Population

The study population consists of patients who had claims between 2016 and 2024 for antiretroviral (ARV) medications approved by the Food and Drug Administration (FDA) for PrEP. Data on PrEP use are available from all 50 states, Washington, DC, and Puerto Rico. Objective 1 will use descriptive and exploratory assessments to contextualize PrEP scale-up. Objective 2 will compare trends in jurisdictions implementing a particular program versus a control group of jurisdictions not implementing that program. Selection of control jurisdictions will vary depending on the level of analysis: for instance, state-level analyses may include all states, whereas analyses at the county level may include counties that are matched by relevant characteristics such as HIV prevalence or county size. Data will be analyzed retrospectively from January 1, 2016, to December 31, 2024, and we will incorporate 4 future annual data updates for the years 2025 to 2028. This study period was selected because the PrEP dataset was considered by the data provider to be internally consistent in the way it was received from pharmacies over the time period, and allows for sufficient time before the launch of EHE programs in 2019. Objective 3 will model program effects for all EHE jurisdictions on future PrEP use based on an up to 20-year time horizon, expanding our team’s existing models for 6 EHE jurisdictions [18,19].

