**Primary outcomes**							
	PrEP starts	New PrEP users in each jurisdiction per time period		National PrEP database		PrEP initiation/population	
	PrEP start needs	New PrEP users, ratio-to-need in jurisdiction per time period		National PrEP database		PrEP initiation/HIV diagnoses	
	PrEP retention	User retained in care per time period		National PrEP database		Average retention time/population	

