**External clinical programs**			
	Safety-Net PrEP Clinic	Delivery of PrEP through an existing STI^d^ clinic, community health center, pharmacy, or similar public health clinic, aimed at expanding PrEP access among key populations through reduced cost or free services	
	Telemedicine PrEP	Consists of full or hybrid telemedicine PrEP services that reduce or eliminate the need for in-person clinical visits	
	PrEP Assistance Program	Cover the cost of PrEP-related services, either directly or indirectly, usually by reimbursing providers for clinical visits and lab tests, or paying PrEP-related out-of-pocket costs to health plans	
	PrEP navigation services	Provide assistance to find a PrEP provider and address barriers to access PrEP, as well as support strategies to facilitate retention or reinitiation into PrEP care	

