To understand the impact of PrEP policies and programs (objective 2), we will leverage the legal coding and health jurisdiction program provision datasets described above to conduct quasi-experiments with outcomes of PrEP starts, PnR, and retention in care. PrEP programs have been adopted by local health authorities in the context of the disbursement of EHE funds as grants to applicants. Despite the lack of random assignment of jurisdictions to policies and programs, we propose a quasi-experimental design that allows us to have findings that reflect several of the characteristics of randomized studies, including temporality and controlling for time-invariant factors. Although quasi-experimental approaches are subject to some limitations inherent to nonrandomized designs such as challenges in controlling for time-varying characteristics, these designs minimize bias relative to other analysis approaches. Moreover, quasi-experimental approaches improve upon the external validity of randomized studies because the data stem from programs that have been enacted in practice. Because of the study design, results will be well positioned to inform real-world programs such as those that comprise EHE efforts. For quasi-experiments, we will conduct analyses using methods such as difference-in-differences (DID) that account for intervention and control jurisdiction trends before program implementation. Because interventions are implemented at different points in time, we will use the heterogeneous DID method proposed by Callaway and Sant’Anna [32] or a similar method to account for potential confounding from multiple implementation periods. Health jurisdictions implementing a program or policy will be the primary intervention unit, and controls will be jurisdictions not implementing a program. DID analyses will be accomplished with regressions that include a term for group (eg, telemedicine PrEP program or not), period (month), and group-by-period interactions that serve to estimate the effect of the intervention. Our approach provides a relatively large sample size for such analyses, with many of the 50 counties or local jurisdictions funded under the EHE program implementing programs under assessment, and other non-EHE jurisdictions also implementing some of the identified programs. Control jurisdictions will be counties or states in the United States that do not implement a particular program, using 9 years of monthly PrEP use data (2016-2024). Depending on characteristics of the intervention, such as statewide provision, we may restrict the control group to jurisdictions meeting certain criteria in order to improve the match between intervention and control groups. For instance, we might match counties by HIV prevalence or jurisdiction size.

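### PrEP starts mix new users with restarts, contrary to Table 1, and the monthly series from January 2016 has no look-back, so existing users enter as starts in its first months

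*Protocol article*

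**What the plan says.** The article describes the starts outcome in two places. In Table 1, under primary outcomes, it is "New PrEP users in each jurisdiction per time period", computed as initiation over population. Under Primary Outcome Measures, for monthly assessments, "a PrEP start is defined as a person initiating PrEP for the first time or reinitiating PrEP after a lapse in prescription", the lapse being "of a cut point, such as at least 1 month, calculated from the biweekly proportion of days covered (PDC) reaching 0.57 or lower". One month is given as an example, and the article adds: "We will conduct sensitivity analyses to assess the impact of different cut points for lapses in coverage".

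Retention is the complement of starts: "all PrEP fills not classified as PrEP starts will be considered prescriptions obtained while retained in PrEP care". It is also a primary outcome in Table 1 in its own right, and Data Analyses says objective 2 will "conduct quasi-experiments with outcomes of PrEP starts, PnR, and retention in care".

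On timing, Research Setting and Population states: "Data will be analyzed retrospectively from January 1, 2016, to December 31, 2024". Data Analyses commits the objective 2 comparisons to nine years of monthly data, 2016 to 2024, so no month is set aside to identify people already on PrEP. Supply carried over from the previous year is addressed only for the yearly count of users.

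**The concern.** There are two separate problems.

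**Restarts.** Every fill is either a start or a retained fill. Preventing a lapse therefore removes a possible later restart from the starts count. A program that keeps people on PrEP, and changes nothing else, looks worse on starts. Table 2 shows why this matters: navigation services include "support strategies to facilitate retention or reinitiation into PrEP care". Those two aims push the combined count in opposite directions, so for that program type a change in starts cannot be read without its components. Table 1 tells the reader that restarts are not in the count at all.

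**Existing users in early 2016.** Whether a fill is someone's first is judged only within data that begin on 1 January 2016. A person on PrEP through 2015 has a first observed fill in early 2016 and is recorded as a start. The size of this spike follows each county's existing user base, so it differs between program and control counties and lies at the beginning of the period used to judge parallel trends.

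Varying the lapse cut point addresses neither problem. Any cut point still mixes restarts with first starts, and none adds look-back.

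**Working it through.** The article gives no figure for either effect, so there is nothing to reproduce. Both sizes below rest on stated assumptions.

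**1. The lapse rule.** In a two-week window, 7/14 = 0.50 meets the 0.57 cut and 8/14 = 0.571 does not. Seven or fewer covered days qualify, which agrees with the article's gloss of fewer than 4 days per week. How biweekly windows add up to one month is not fixed.

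**2. Effect of preventing lapses on combined starts.**

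Assumptions (none is in the article): first-time starts are constant at 20 per month; monthly lapse hazard h is 5 to 15%; a share r of lapsers (30 to 60%) eventually returns, at 20% of the waiting pool per month; the program cuts h by 20% and leaves first-time starts unchanged.

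- Baseline users U = 20 / [h(1 − r)]. Baseline restarts per month = hUr. Combined starts = 20 + hUr.
- Example with h = 0.10, r = 0.5: U = 20/0.05 = 400; restarts = 0.10 × 400 × 0.5 = 20; combined starts = 40 per month.
- After the program, running users and the lapsed pool forward month by month, combined starts average 38.1 per month over year 1: 38.1/40 − 1 = −4.8%. Users reach 446.8 at month 12: 446.8/400 − 1 = +11.7%.

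| h | r | Starts, year 1 | Starts, months 13–36 | Starts, about month 80 | Users, month 12 |
|---|---|---|---|---|---|
| 0.05 | 0.3 | −3.2% | −3.4% | −0.8% | +8.1% |
| 0.05 | 0.6 | −6.5% | −8.1% | −3.6% | +6.4% |
| 0.10 | 0.5 | −4.8% | −4.4% | −0.7% | +11.7% |
| 0.15 | 0.3 | −2.5% | −1.4% | 0.0% | +16.9% |
| 0.15 | 0.6 | −5.2% | −4.4% | −0.6% | +13.9% |

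First-time starts alone change by 0% throughout. The fall fades because a larger user base later produces more lapses and returns.

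**3. Existing users counted as starts.**

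Inputs: growth of 56% per year for 2012 to 2017 (Introduction). Assumptions: mean duration D of 6 to 12 months, and every user on PrEP on 1 January 2016 refills within the first quarter.

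- Continuous monthly growth g = ln(1.56)/12 = 0.0371.
- True monthly starts per existing user s = g + 1/D.
- True starts over the first quarter = s(e^(3g) − 1)/g = 3.173s; over 2016 = s(0.56)/g = 15.11s.
- The misclassified stock is 1, so inflation = 1 + 1/(true starts).

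| D (months) | s | First quarter | All of 2016 |
|---|---|---|---|
| 6 | 0.2037 | 1 + 1/0.646 = 2.55 | 1 + 1/3.079 = 1.32 |
| 9 | 0.1482 | 1 + 1/0.470 = 3.13 | 1 + 1/2.239 = 1.45 |
| 12 | 0.1204 | 1 + 1/0.382 = 3.62 | 1 + 1/1.819 = 1.55 |

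How long it lasts depends on days' supply. With 30-day fills the whole excess falls in January; with 90-day fills it spreads over January to March. From month 4 there is none: by then existing users have refilled, and someone returning after a lapse counts as a start under the article's rule anyway.

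**The case against.** The case for leaving the plan alone has real force.

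- Counting restarts is openly stated, the one-month lapse is only an example, and cut points will be varied. Dropping restarts altogether would deny credit to programs that aim at reinitiation. This stands, and is why the combined count should be kept beside its components.
- Retention is a separate primary and objective 2 outcome, and reinitiation over time is to be explored under objective 1. A lapse-preventing program would show its benefit there. This stands: the problem is with starts read alone.
- A reader might infer that the definition reverses the sign for navigation programs. The documents do not support that. Table 2 says navigation also helps people find a provider, which may raise first starts; reversal needs assumed restart shares and little gain in new users.
- A reader might also infer that program effects are generally biased by the 2016 spike, or that all of 2016 must be discarded. Neither follows. Month terms absorb the common part of the spike. A Callaway-Sant'Anna estimate uses the last pre-treatment month as base, so a January-to-March 2016 excess does not reach the effect of a program launched later.
- A look-back rule may sit in a fuller plan that is not shown. That is possible. But the article commits the monthly comparisons to the whole of 2016 to 2024, and the conflict between Table 1 and the outcome text is within the article itself.

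**Conclusion.** The point holds in a limited form. Table 1 and the outcome section define starts differently, and that needs no assumption. The restart rule lowers combined starts by about 2.5 to 6.5% in year 1 for a program that only cuts lapses by 20%, fading over several years, while use and retention improve. This size rests entirely on assumed lapse and return rates.

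The missing look-back inflates first-quarter 2016 starts by about 2.5 to 3.6 times, given durations of 6 to 12 months and the article's growth rate, and is confined to roughly the first 1 to 3 months. A steady-state calculation would give 3 to 5 times ((3 + D)/3), but it ignores the growth that the article reports. What survives the month terms is the part that differs by county. It can affect early event-study leads, the Granger check, placebo dates that fall early in the series, pre-period matching or synthetic control, and any group-by-period regression that averages all pre-program months. It does not affect a Callaway-Sant'Anna effect whose base month lies after the spike. The article names that method or a similar one and also describes the regression form, so this protection is not assured for every analysis.

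**What to change.** 1. Use the first 3 to 4 months of 2016 only to identify people already on PrEP, and begin the monthly starts series after them.
2. Report first-observed starts and restarts as separate components alongside the combined count, for every objective 2 analysis of starts.
3. Add a sensitivity analysis with a longer look-back, for example 12 months. First-observed does not mean first-ever: someone who used PrEP before 2016 and returned after the look-back would still appear as new.
4. Align Table 1 with the outcome section, including the ratio-to-need row, which also refers to new users.

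Cost: minor recoding of one variable from data already held. The main series keeps 32 or 33 of the 36 months before 2019 (36 − 4 or 36 − 3). The 12-month sensitivity analysis keeps 24, which is a reason not to make it the main definition.

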#### Data Analyses

We plan to conduct analyses that explore trends in PrEP use over time, reveal the impact of programs and policies, and assess the long-term impact of policies and programs, including health and cost-effectiveness.

To understand PrEP use over time (objective 1), we will include current and new PrEP formulations to explore patterns regarding the growth of PrEP use, changes in retention in PrEP care over time, reinitiation of PrEP over time, and associations with changes in PrEP use. These exploratory assessments will be conducted largely with descriptive and regression analyses, and we anticipate new analyses will emerge as the prevention landscape develops. One area of potential analysis involves characterizing the long-term users of PrEP services, seeking to explore differences between those able to maintain long-term PrEP use versus those with shorter periods of PrEP use. This analysis would likely be largely descriptive and supplemented by regression models. Other analyses may be specific to the PrEP modality. For instance, analyses of injectable PrEP modalities may look at associations between their use and type of insurance coverage, socioeconomic characteristics of users, prior PrEP use patterns, and service provider locations.

To understand the impact of PrEP policies and programs (objective 2), we will leverage the legal coding and health jurisdiction program provision datasets described above to conduct quasi-experiments with outcomes of PrEP starts, PnR, and retention in care. PrEP programs have been adopted by local health authorities in the context of the disbursement of EHE funds as grants to applicants. Despite the lack of random assignment of jurisdictions to policies and programs, we propose a quasi-experimental design that allows us to have findings that reflect several of the characteristics of randomized studies, including temporality and controlling for time-invariant factors. Although quasi-experimental approaches are subject to some limitations inherent to nonrandomized designs such as challenges in controlling for time-varying characteristics, these designs minimize bias relative to other analysis approaches. Moreover, quasi-experimental approaches improve upon the external validity of randomized studies because the data stem from programs that have been enacted in practice. Because of the study design, results will be well positioned to inform real-world programs such as those that comprise EHE efforts. For quasi-experiments, we will conduct analyses using methods such as difference-in-differences (DID) that account for intervention and control jurisdiction trends before program implementation. Because interventions are implemented at different points in time, we will use the heterogeneous DID method proposed by Callaway and Sant’Anna [32] or a similar method to account for potential confounding from multiple implementation periods. Health jurisdictions implementing a program or policy will be the primary intervention unit, and controls will be jurisdictions not implementing a program. DID analyses will be accomplished with regressions that include a term for group (eg, telemedicine PrEP program or not), period (month), and group-by-period interactions that serve to estimate the effect of the intervention. Our approach provides a relatively large sample size for such analyses, with many of the 50 counties or local jurisdictions funded under the EHE program implementing programs under assessment, and other non-EHE jurisdictions also implementing some of the identified programs. Control jurisdictions will be counties or states in the United States that do not implement a particular program, using 9 years of monthly PrEP use data (2016-2024). Depending on characteristics of the intervention, such as statewide provision, we may restrict the control group to jurisdictions meeting certain criteria in order to improve the match between intervention and control groups. For instance, we might match counties by HIV prevalence or jurisdiction size.

Although we have conducted substantial outreach to health jurisdictions to optimize engagement, we anticipate that there will be some missing data from the health jurisdiction survey. It is likely not a valid approach to impute data on whether a program was implemented in a particular jurisdiction. Therefore, analyses will be conducted only among jurisdictions providing data. To explore the impact of the missingness, we will assess descriptive differences between missing and nonmissing jurisdictions for the outcome over time and for key sociodemographic variables. Our outcome assessment will include the determination of policy impacts on PnR, an equity metric. Additionally, we will identify potential inequities in PrEP use based on key geographic, socioeconomic, and demographic characteristics. This may be conducted empirically with interaction terms between the policies of interest and these characteristics. DID models assume that trends in the intervention and control groups are parallel before the intervention. This is a critical consideration because control jurisdictions might have additional interventions to the one under consideration. We will seek to assess the validity of this premise, using techniques such as visual assessments of event-study plots and the Granger causality test to determine whether the design is sufficient to meet the parallel trends assumption. If parallel trends assumptions are not met, we will consider alternative approaches such as multivariable matching, lagged dependent variable regression, and synthetic control models (adapted for multiple treated units). The synthetic control method uses a matching algorithm to create a weighted dataset for the control (nonintervention) group, assigning a weight to each element in the group to eliminate prior differences in critical covariates and the outcome. Another option is to use difference-in-difference-in-differences (DDD) to assess the additional change from a specific policy (eg, telemedicine) above and beyond the overall EHE program effect for funded EHE jurisdictions. The nature of the DID and DDD designs controls for confounders that do not vary over time. Therefore, to optimize model efficiency, we will not control for variables expected to remain constant over time (eg, area-level poverty), only adding time-variant covariates. To further ascertain the validity of the DID approach, we will conduct placebo tests for policies that our models have found to have statistically significant effects on PrEP use. These tests assign earlier implementation dates selected at random (eg, false) to treated units to observe if we continue to reject the null hypothesis under these “false” implementation dates. Statistically insignificant results from the placebo tests will increase confidence that the model outcomes are valid. Further, we will assess the sensitivity of our models to the implementation time period by conducting the Bacon-Goodman [33] decomposition and reporting any disproportionate influence of certain implementation periods. We will seek to conduct additional sensitivity analyses that explore whether funding levels determine the impact of programs, with the program intervention variable being related to prevention budget expended rather than whether the program was enacted. Analyses will be conducted in SAS 9.4, STATA 19, or similar software. Given that there are multiple policies, it will be critical to address challenges with multiple comparisons. To accomplish this, we will, where possible, seek unified model approaches that simultaneously test the effects of multiple programs.

To assess the impact of scaling-up different PrEP programs and policies investigated in health jurisdictions (objective 3), we will use a previously published mathematical model leveraging the estimates of the effectiveness and cost of each policy and program from DID analyses to inform our models. The Localized Economic Modeling (LEM) platform is a dynamic compartmental HIV transmission model used to simulate changes in HIV epidemics. Populated with locally sourced data on demographic, epidemiological, and policy conditions for specific jurisdictions, the model has been previously applied to evaluate combination implementation strategies for EHE in 6 US cities: Atlanta (Georgia), Baltimore (Maryland), Los Angeles (California), Miami (Florida), New York City (New York), and Seattle (Washington) [18,19,34-37]. The model stratifies the study population by biological sex, race and ethnicity (non-Hispanic Black, Hispanic or Latino, non-Hispanic White, and other), HIV transmission risk group (men who have sex with men, people who inject drugs, and heterosexuals), and sexual risk behavior intensity (high- or low-risk). The adult population is followed from susceptibility to HIV infection through seroconversion, diagnosis, and treatment with antiretroviral therapy (ART), accounting for observed disparities in access to HIV health services, including HIV testing, ART, PrEP, and harm reduction services. The LEM has been applied to evaluate various public health interventions related to EHE and their health impacts [36,38,39]. As part of ongoing efforts, we are expanding and updating the underlying evidence while adapting and recalibrating the model for all 48 EHE priority counties and Washington, DC (not including San Juan, Puerto Rico, and the 7 EHE priority states with high HIV incidence in rural areas). The updated models will be leveraged to examine incident HIV infections averted, incremental costs, gains in quality-adjusted life years (a composite measure capturing HIV-related morbidity, mortality, and transmission) [40], cost-effectiveness, and health impacts (measured by disparities in HIV incidence) of the effective PrEP scale-up programs or policies identified in objective 2—compared to a “status quo” scenario assuming no further efforts to scale-up access to PrEP. We will perform the modeling analysis of PrEP programs and policies up to 20-year time horizon, evaluating them both individually and in combination to capture their long-term health and economic impacts in different jurisdictions, as well as potential synergistic effects between programs and policies. Analyses will be conducted according to best practices guidelines in simulation modeling [41] and cost-effectiveness analysis [42].

#### Power Calculation: Objective 2

The study design achieves 90% power to detect a minimum difference between intervention and control county PrEP rate means of 2.4 PrEP starts per 100,000 population. This is based on a sample size of 8,784,000 county-person-month observations, a figure obtained from a minimum estimate of 6 counties implementing a particular program and 238 control counties not implementing the program. We assume that each county has an average of 300 individual PrEP users (a conservative estimate because the 2021 average and median county PrEP users are 1210 and 482), and we assume an average of 60 months of follow-up (a conservative estimate because the total follow-up period is 144 months). The standard deviation of PrEP use at the county level is 73, and we conservatively assumed a small (0.05) within-person correlation. The power assessment is based on a time-by-treatment interaction test using a mixed-model analysis with a significance of 0.05. We performed a similar analysis for state-level policies and found a minimum detectable difference of <3 additional PrEP starts. Power calculations were performed in PASS 2022.

